## Abstract

**Background:**

Community-based services such as telephone support lines can provide valuable informational, emotional, and practical support for cancer patients via telephone- or Web-based (live chat or email) platforms. However, very little rigorous research has examined the efficacy of such services in improving patient outcomes.

**Objective:**

This study will determine whether: proactive telephone or Web-delivered support produces outcomes superior to printed information; and Web-delivered support produces outcomes comparable to telephone support.

**Methods:**

A consecutive sample of 501 lung cancer outpatients will be recruited from 50 Australian health services to participate in a patient-randomized controlled trial (RCT). Eligible individuals must: be 18 years or older; have received a lung cancer diagnosis (including mesothelioma) within the previous 4 months; have an approximate life expectancy of at least 6 months; and have Internet access. Participants will be randomly allocated to receive: (1) an information booklet, (2) proactive telephone support, or (3) proactive Web support, chat, and/or email. The primary patient outcomes will be measured by the General Health Questionnaire (GHQ-12) and Health Education and Impact Questionnaire (heiQ) at 3 and 6 months post recruitment. The acceptability of proactive recruitment strategies will also be assessed.

**Results:**

It is hypothesized that participants receiving telephone or Web support will report reduced distress (GHQ-12 scores that are 0.3 standard deviations (SD) lower) and greater self-efficacy (heiQ scores that are 0.3 SDs higher) than participants receiving booklets. Individuals receiving Web support will report heiQ scores within 0.29 SDs of individuals receiving telephone support.

**Conclusions:**

If proven effective, electronic approaches such as live-chat and email have the potential to increase the accessibility and continuity of supportive care delivered by community-based services. This evidence may also inform the redesigning of helpline-style services to be effective and responsive to patient needs.

## Introduction

### Background

Cancer is one of the leading causes of disease-related burden in Australia. Lung cancer is the fourth most incident cancer and approximately 10,300 cases were diagnosed in 2014 [1,2]. Lung cancer mortality rates are relatively higher than other cancer types, with only 6% of those diagnosed with small cell lung cancer surviving 5 years post diagnosis [3]. Lung cancer patients and survivors also report a wide array of physical and psychological issues and, when compared with 6 other common cancer types, report significantly higher levels of clinically significant anxiety and depression [4-6]. Despite the clear evidence-based imperative for providing supportive care to lung cancer patients to maximize their quality of life, this group is under researched in terms of supportive care [7].

Generally, cancer patients report dissatisfaction with the amount and type of information provided regarding management of their health, the failure of health care providers to attend to or offer referral for psychosocial needs, and poor coordination of services [8]. These experiences can exacerbate patients’ suffering. With health care resources stretched to capacity, there is an urgent need to assess the potential benefits of alternative modes of service delivery. These modes may include services provided by community-based organizations rather than hospitals or physicians; and telephone-based or Web platforms rather than the relatively costly and less accessible face-to-face options. However, despite the evidence of their need for support, lung cancer patients are underrepresented in the overall profile of community cancer support service users [9]. Proactive strategies for engaging this vulnerable group with alternative community-based services may provide a valuable opportunity to enhance lung cancer care, particularly in providing information and support in managing the debilitating consequences of diagnoses and treatments.

There is substantial evidence that intensive psychological strategies have been associated with improved psychological health and quality of life in cancer patients [10]. A common example of an intensive strategy is cognitive behavior therapy (CBT) in which adaptive coping elements such as emotional support, positive reframing, planning, acceptance, and support seeking are incorporated into care. A Cochrane review of supportive care interventions including psychotherapeutic interventions and nurse-led counseling improved the emotional, psychological, and physical states (ie, dyspnea) of lung cancer patients [11]. In contrast, relatively little rigorous research has examined the effects of less-intensive forms of supportive care provision for cancer patients [12]. These less-intensive forms of counseling may be delivered by community-based telephone helplines, whereby, unlike hospital-based services, individuals do not receive face-to-face counseling from health professionals familiar with their current care; may have a focus on practical or informational support; and may be a singular encounter.

The Cancer Information and Support (CIS) line is a cancer-specific telephone-based service operated by each state-based Cancer Council in Australia via a national telephone number; the same model operates within the United Kingdom and United States [9,13,14]. The service is staffed by experienced health professionals and provides free, confidential support related to informational, emotional, and practical concerns based on a brief, integrative model of care. A recent review found that telephone-based follow-up care conducted by an experienced nurse was acceptable to patients, cost-effective, and at least equivalent to traditional face-to-face follow-up care in meeting patients’ needs [15]. Hence, telephone delivery means that individualized services can be provided to a broad cross-section of cancer patients in a timely fashion while minimizing cost, logistic, and system barriers [16].

Although telephone-delivered supportive care services, including the CIS, have undergone evaluation of patient use, satisfaction, and acceptability, very little rigorous research has been directed toward understanding the real-world effects of low-intensity models, such as the provision of information, emotional support, and practical support in improving cancer patients’ outcomes [14,17-19]. A systematic review identified only 4 randomized controlled trials (RCT) of similar services with conflicting results reported [20]. One RCT provided evidence of efficacy in that phone-based education and social support delivered by research assistants resulted in reduced mood disturbance compared with mailed education [21]. The remaining 3 trials did not find a significant effect on psychosocial outcomes including distress, anxiety, or depression [22-24]. None of these trials were conducted with lung cancer patients.

While telephone-based support is the traditional mode of delivery of these services, some services are seeking to or have recently included parallel forms of Web support [9,25]. These technology-based approaches are perceived to be accessible, safe, flexible, and anonymous by patients [26-28]. Automated electronic platforms for the delivery of intensive psychological therapies (eg, CBT) have also been found to be effective in reducing anxiety and depression [29]. However, a review by Gustafson et al [30] identified mixed effects when information and support for breast cancer patients was delivered via automated, electronic formats. For community-based services, establishing the efficacy of Web support can provide much needed guidance for deciding if this mode of support should be included as part of the suite of services provided.

In the context of the CIS service, the most appropriate first step for testing Web approaches may be via a proactive and personalized, rather than automated, version of the service through email and live chat. Email counseling involves the patient and counselor exchanging questions and responses at the frequency of their choosing over the Internet. Live chat involves typed interactive conversations occurring in real-time over the Internet. Evidence for online peer-support forums and email is promising with a RCT of a multicomponent Web intervention reporting decreased global severity scores in a sample of 325 breast and prostate cancer patients [31]. However, there is no literature regarding Internet-delivered versions of low-intensity community-based support akin to that offered by the CIS service. For example, a Cochrane review examining the effects of email and Web-messaging between patients and health professionals was unable to establish the benefits of such Web-based platforms due to the lack of high-quality studies identified [32]; relevant to this study, none of the 9 reviewed articles included cancer samples.

This multisite, blinded, patient-RCT will be the first to conduct a robust study of the relative merits of telephone- versus Web-based methods for providing low-intensity information and support to people affected by cancer. Newly diagnosed lung cancer patients will be recruited by health professionals and randomly-allocated on a 1:1:1 ratio to 1 of 3 arms: (1) a printed information booklet, (2) proactive telephone-delivered support, or (3) proactive Web-delivered support. The Consolidated Standards of Reporting Trials of Electronic and Mobile HEalth Applications and onLine TeleHealth is used to describe this study [33].

### Aims

The aims of this study are to identify among a group of newly diagnosed lung cancer patients, if: (1) information and support provided either electronically (email and live chat) or by telephone following active recruitment can produce psychosocial outcomes, which are superior to those achieved by minimal ethical care (a printed *‘Understanding Lung Cancer’* information booklet), and (2) information and support provided electronically can produce psychosocial outcomes, which are comparable to those achieved by a telephone approach.

Intervention effectiveness will be measured by changes in 2 primary outcomes: General Health Questionnaire-12 (GHQ-12) and Health Education Impact Questionnaire (heiQ) scores from baseline to 3 and 6 months post recruitment. Higher GHQ-12 scores represent greater distress; once standardized, higher heiQ scores indicate better functioning as a result of improved self-efficacy and health literacy.

### Hypotheses

It is hypothesized that at 6 months follow-up: (1) those in the 2 experimental conditions (proactive telephone-delivered or Web-delivered support) will have GHQ-12 scores that are 0.3 of a standard deviation (SD) lower than those for the control condition and heiQ scores that are 0.3 of a SD higher than those for the control condition, and (2) those in the proactive Web-delivered support condition will have heiQ scores within 0.29 of a SD of those in the proactive telephone-delivered support condition.

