### Sample Size

The sample size calculation is based on the post-hoc contrasts. The comparison of each intervention group with minimal ethical care is a superiority analysis, whereas the comparison of the 2 intervention arms of the study is a noninferiority analysis.

The study aims to recruit 501 subjects, and therefore complete data will be available for approximately 375 patients (125 per arm) at 6 months with an estimated 25% (125/501 participants) lost to follow-up. This sample size will provide the study with more than 80% power to detect a difference between each of the intervention groups and the control group of 0.35 SD at an alpha level of 0.01 assuming the correlation between baseline and follow-up scores is at least 0.7. This sample size will also provide the study with 90% power to claim noninferiority in the comparison between the 2 interventions if the true underlying difference between the groups is 0.29 SDs for either the heiQ or GHQ-12. A meta-analysis of Web-based emotional support reported an average effect size of approximately 0.4 across 15 studies [48]; similarly, previous research found modest effect sizes of 0.3-0.5 on the heiQ in self-management interventions in Australian and hospital-based samples [49,50]. The age group and gender of nonparticipants will be compared with that of participants to assess nonconsent bias.

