## Results

It is hypothesized that participants receiving telephone or Web support will report reduced distress and greater self-efficacy than participants receiving booklets. Furthermore, individuals receiving Web support will report heiQ scores within 0.29 SDs of individuals receiving telephone support. Participant recruitment is underway and will conclude in September 2017.

This study has been approved by the Hunter New England Human Research Ethics Committee (NHMRC Committee Code: EC00403; Reference No. 14/05/21/4.03); the University of Newcastle Human Research Ethics Committee (NHMRC Committee Code: EC00144; Reference No. H-2014-0240); and, the Cancer Council of New South Wales (NHMRC Committee Code: EC00345; Reference No. 291). The study has also been approved by local research governance committees at each participating health service. This trial was registered with the Australian New Zealand Clinical Trials Registry (ACTRN12615000932561) and received funding from the National Health and Medical Research Council as a Partnership Project.

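### Hypothesis 2 bounds Web versus telephone on both sides at 0.29 SD if read literally, while the Sample Size section makes it a one-sided noninferiority comparison

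*Protocol article*

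**What the plan says.** The protocol article describes the Web-versus-telephone comparison in several places.

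- **Introduction, Hypotheses.** Hypothesis 2 expects Web support to give "heiQ scores within 0.29 of a SD of those in the proactive telephone-delivered support condition". It names heiQ only and gives no direction.
- **Abstract, Results, and the main Results section.** Both repeat the criterion. The main section has "individuals receiving Web support will report heiQ scores within 0.29 SDs of individuals receiving telephone support".
- **Introduction, Aims.** Aim 2 looks for "psychosocial outcomes, which are comparable to those achieved by a telephone approach". The Objective in the Abstract also uses the word comparable. Neither gives a side.
- **Methods, Sample Size.** After calling the comparisons with control superiority analyses, the text continues "whereas the comparison of the 2 intervention arms of the study is a noninferiority analysis". It then claims "90% power to claim noninferiority in the comparison between the 2 interventions", conditional on the following: "if the true underlying difference between the groups is 0.29 SDs for either the heiQ or GHQ-12".
- **Methods, Statistical Analysis.** The third contrast compares the two intervention arms, with a Bonferroni correction. No margin or side is attached to it.

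**The concern.** A difference that lies within 0.29 SD is, in ordinary meaning, neither more than 0.29 SD worse nor more than 0.29 SD better. Noninferiority asks only that Web is not worse by more than the margin. The second aim of the trial therefore carries two criteria.

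They agree when Web is the poorer arm. They differ when Web is the better arm: a clear Web advantage meets noninferiority easily but may not satisfy the literal hypothesis. If both wordings stay in print, the conclusion on aim 2 could be argued either way once the data are known. The stated power also belongs to one of the two criteria only.

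The complaint is not that an article leaves out a detailed decision rule, which may properly sit in a fuller document. It is that the article states the criterion in two ways that disagree.

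**Working it through.** **Inputs from the Sample Size section:** 125 completers per arm; correlation between baseline and 6-month scores of 0.7 (stated in the superiority sentence and assumed to carry over); 0.29 SD. Analysis of covariance comes from the Statistical Analysis section.

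**Assumptions not in the document:** one-sided level 2.5%, because no level or sidedness is given for noninferiority (the stated 0.01 belongs to the superiority contrasts); 0.29 SD used as the margin; true difference 0; normal approximation.

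**Standard error of the adjusted difference, in SD units**

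SE = √[(2/125) × (1 − 0.7²)] = √(0.016 × 0.51) = 0.0903

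**Reproducing the stated 90%**

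Noninferiority power = Φ(0.29/SE − z) = Φ(3.210 − 1.960) = Φ(1.250) = 89.4%

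This agrees with the stated 90%; exactly 90% would take 128 per arm. With a correlation of 0 instead of 0.7 the figure would be 63%, so the 0.7 does appear to carry over.

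**The same inputs read as equivalence (two one-sided tests, ±0.29 SD, true difference 0)**

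Power = 2Φ(0.29/SE − z) − 1 = 2 × 0.8944 − 1 = 78.9%

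Reaching 90% would need about 158 completers per arm.

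**Dependence on the level**

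| Level per side | Noninferiority | Equivalence |
|---|---|---|
| 5% | 94.1% | 88.3% |
| 2.5% | 89.4% | 78.9% |
| 1% | 81.2% | 62.3% |
| 0.5% | 73.7% | 47.4% |

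**Where the two criteria split the same data (2.5% per side)**

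Confidence interval half-width = 1.96 × 0.0903 = 0.177 SD

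- Noninferiority on heiQ needs an observed Web minus telephone difference above −0.29 + 0.177 = −0.113 SD.
- Establishing a difference within 0.29 SD also needs it below 0.29 − 0.177 = +0.113 SD.

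Example: Web observed 0.15 SD better gives 0.15 ± 0.177, an interval of −0.03 to 0.33. Noninferiority is shown; a difference within 0.29 SD is not. If Web is truly 0.10 SD better, the chance of meeting noninferiority is 99.1% and of meeting equivalence 54.8%.

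**The power sentence taken literally**

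If the true difference is 0.29 SD with Web the worse arm, and 0.29 SD is also the margin, power = Φ(0 − 1.96) = 2.5%, which is alpha. The 90% is recovered only when 0.29 SD is the margin and the true difference is 0.

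**The case against.** The strongest reply is that the analysis type is stated. The Sample Size section is the only place that classifies this comparison. It says noninferiority twice and sets it against the superiority contrasts. The hypotheses say what the investigators expect; they are not decision rules. Hypothesis 1 expects scores 0.3 SD lower or higher than control, and nobody would call a 0.5 SD benefit a failure of it. The word comparable is compatible with noninferiority, and the document does not use the word equivalence for the outcome comparison.

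Much of this stands. A reader might infer that the protocol sets a formal two-sided equivalence test as its success rule, so that a Web advantage would count as failure. The document does not support that: it gives no such rule, and the two-sided bound comes only from the literal sense of the wording.

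A reader might also infer that the 90% power is wrong, or that it can hold only for noninferiority. That is not supported either. The 90% is claimed expressly for noninferiority and is reproduced as such. The gap between 89% and 79% rests on an assumed level: at 5% per side equivalence is within two points of 90%, and at 1% neither criterion reaches 90%.

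What the reply does not remove is the disagreement in wording. Hypothesis 1 gives directions and hypothesis 2 gives none. Its undirected form appears in three places, and the Statistical Analysis section does not resolve it.

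**Conclusion.** The point holds as an inconsistency in how the Web-versus-telephone criterion is stated, and it should be corrected because it touches a main aim. Noninferiority is the likelier intention.

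Its practical size is the range of results on which the two wordings disagree: observed Web advantages above about 0.113 SD, given 125 per arm, a correlation of 0.7 and an assumed one-sided 2.5% level. If equivalence were really meant, power at a true difference of 0 would be about 79% at that level, 88% at 5% per side and 62% at 1% per side.

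Two related faults in the Sample Size section belong to the same correction. It words 0.29 SD as the true difference, where its figure works only with 0.29 SD as the margin. It also covers heiQ or GHQ-12, where hypothesis 2 names heiQ alone.

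**What to change.** 1. **Hypothesis 2 (Hypotheses, Abstract Results, main Results).** Reword as noninferiority: Web is not worse than telephone by more than 0.29 SD. On heiQ, where higher is better, the lower confidence limit for Web minus telephone must lie above −0.29 SD. If GHQ-12 is covered, as the Sample Size section says, the upper limit must lie below +0.29 SD, because higher GHQ-12 scores mean more distress.
2. **Abstract Objective and Aims.** Replace comparable with wording that says not inferior.
3. **Sample Size.** Name 0.29 SD as the margin, with an assumed true difference of 0. State the one-sided alpha after any Bonferroni correction and the power that goes with it. The 90% fits a one-sided 2.5% level; at 1% it would be about 81%.
4. **If equivalence is really meant,** change the Sample Size section to an equivalence analysis and restate the power for the chosen alpha.

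The first three changes are wording and one power statement, with no new patients or data. Under the fourth, the stated power becomes less favourable, or the number of completers rises (about 158 per arm for 90% at 2.5% per side).

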## Methods

### Care Coordinator, Nurse, and Clinician Recruitment

As of June 1^st^, 2016, care coordinators, nurses, and clinicians from 50 health services were committed to participating in the study. A variety of recruitment techniques were used. Care coordinators, nurses, and physicians also received study information with a link to a Web-based expression of interest (EOI) form via several national professional organizations such as: the Lung Foundation Australia; the Clinical Oncology Society of Australia; the Medical Oncology Group of Australia; and the Thoracic Society of Australia and New Zealand. Contacts were also identified through publicly available lists of multidisciplinary teams or through personal connections with research team members. Wherever possible, individuals received a personalized email with an embedded link to the EOI form.

The research team contacted individuals who completed a Web-based EOI and arranged a teleconference to gauge capacity and willingness to participate in the study. No specific exclusion criteria related to the size or location of the health service were applied in order to represent the diversity of rural and urban settings in which lung cancer patients may receive care.

### Study Setting

All interventions will be delivered through 1 state-based CIS service, the Cancer Council New South Wales (CCNSW). In usual practice, clients would be automatically connected to the CIS service in their state of residence. A study-specific telephone number and email address will be set up to permit isolation of study participants from other CIS clients. A directory of state-specific services will be created to ensure participants from areas outside of New South Wales can receive the information relevant to their local areas.

CIS consultants are qualified oncology and/or psychosocial health professionals (ie, nurses, social workers, counsellors). Consultants receive extensive training in supportive care principles and therapeutic communication skills. As part of their ongoing training, consultants routinely participate in clinical supervision and professional development workshops; furthermore, a sample of calls are regularly reviewed by a service manager as part of performance evaluations. A total of 6 CIS consultants will participate and are trained to deliver both the telephone- and Web-based interventions.

